**Figure 1 F1:**
[figure not shown]
**Study Design**
.

Traditional RCT methodology supports a single primary outcome measure, but a theoretical framework for outcome evaluation was based on the conceptual framework of technology-based KT [68,69]. Therefore, indicators of intervention effectiveness for this study are as follows:

1. Use of technology (structural evaluation): Embedded tracking will record the retrieval behavior (frequency of access; number of pain studies retrieved).

2. Perceived usefulness (subjective evaluation): Users will respond to randomly embedded judgments about the usefulness of their session experience.

3. Skills/behaviors in accessing information: An observational test of information-searching behaviors measuring how different professions access evidence for specific clinical questions and the type, quality, and usefulness of evidence retrieved.

4. Application: Evidence-based decision making

a. Participants’ EBP behaviors and decision making will be measured by a standardized self-report scale.

b. Chart-stimulated recall will measure competency for using an evidence-based approach to address problems within participants’ own clinical practice.

Our secondary objective is to evaluate professional differences in access/use of research. Therefore, we will evaluate whether the primary outcome measures—either at baseline or in response to the intervention—are modified by professional group. Further, we will perform a structured classification of the types of studies accessed by different professions to look at variations in the type of evidence valued.

We expect that (1) retrieval and application of pain evidence and satisfaction with evidence resources will improve more with push-out intervention and (2) there will be differences between professions in attitudes towards EBP, response to evidence tools/resources, and types of evidence most accessed.

### Interventions

All participants will receive unique IDs and passwords and will be able to log into an evidence resource, Pain PLUS (Figure 2), to search for recent studies and systematic reviews of pain management (PULL). Once signed up, all practitioners will receive more specific instructions on using the evidence repository. This evidence repository has a cumulative collection of research evidence that has evolved over time—first for medicine, then for nursing, and then rehabilitation and psychology. It contains a searchable database with links to PubMed abstracts and direct links to any free full-text articles.

**Figure 2 F2:**
[figure not shown]
**Pain PLUS Intervention.** Screenshot of the Pain PLUS main webpage.

### PUSH + PULL intervention

Pain PLUS is a customized, personalized, evidence-based, alerting and look-up service that links clinicians to new research findings most relevant to their clinical practice. This service is based on ongoing hand searches of over 120 clinical journals. Trained, experienced research staff determine scientific merit/quality rating. Discipline-specific clinical ratings of relevance and newsworthiness are obtained from volunteer raters who agree to screen abstracts. Raters are in active clinical practice and are recruited from the intervention target group communities (“educational influential”). All study participants will be signed into the *pain* content of the service but can also select email frequency and the cut-off for relevance and quality to control the degree of relevance and frequency of evidence they receive. Their experience will be a customized notification of new research (Figure 3).

**Figure 3 F3:**
[figure not shown]
**Pain PLUS Intervention.** Screenshot of an example Pain PLUS email alert.

### PULL intervention

Users will “see” a similar format when they access the pull intervention, but this “placebo control” website will not include any individualized information, nor will they receive alert emails. This group can access new research but must search for it.

### Randomization

Computerized randomization will allocate individuals to intervention group at three months; crossover is automatic at nine months.

### Study population and recruitment

Eligible practitioners must (1) be physicians, nurses, occupational therapists (OTs), physical therapists (PTs), or psychologists who are currently working in clinical practice at least one day/week; (2) be fluent in English; (3) have access to a computer at home or at work that has unrestricted access to the World Wide Web; and (4) have an active email account. Clinicians who meet the eligibility criteria are enrolled in the study by the research assistant.

### Outcome measures

We will use an evaluation framework developed specifically for technology-enabled knowledge translation [68-70] to evaluate our primary research question on KT effectiveness as outlined below and in Table 1. It is important when evaluating technology to determine whether the technology performs as expected (structural) and in a way that users find useful (subjective) to understand impacts on higher-level outcomes (cognitive and behavioral).

**Table 1 T1:** Overview of Study Assessments

**Elements of evaluation based on a theoretical framework**[68-70]	**What is evaluated**	**Evaluation methods (applied throughout the trial)**
Structural	Technological functionality and design	1. Embedded quick questions on functionality
		2. Number of articles accessed.
Subjective (Usefulness)	Perceived usefulness of intervention	1. Embedded questions on usefulness of randomly selected logins.
Cognitive	1. Attitudes towards the use of evidence in practice	1. Attitudes about EBP from Knowledge/*Attitude*/Behaviour Questionnaire [71]
	2. Types of evidence valued	2. We will code using a taxonomy that addresses type of pain, type of intervention and type of research to look at preferences for information across disciplines.
Behavioral	Behaviour in Applying Evidence in Practice	
	1. Self-reported EBP behaviour	1. Self-reported from Knowledge/ Attitude/*Behaviour* Questionnaire [71]
	2. Research Access Skills	2. Skills at retrieving useful evidence when presented with a clinical question will be assessed by a structured online performance-based test of information access behavior [72]
	3. Application of Research Evidence in Clinical Decision-Making	3. Actual integration of use of evidence in decision-making will be assessed by chart stimulated recall [73-75]

### Structural

Structural usability analysis will have some embedded questions on functionality but will primarily be based on tracking of how the technology is used. We will have data on the number of logins and number of pain and other (specialty) research studies in the database that are accessed. These data will be summarized by the average frequency of use per month and mean number of studies accessed. Other utilization outcomes that will be tracked by the PLUS software include the change in the average frequency of use, average number of keystrokes per month, and the average number of times practitioners use certain specific electronic resources. Collection of these outcomes will be software regulated and, thus, not require any participant burden.

### Subjective

The subjective elements will focus on perceived usefulness of individual sessions. Participants will be asked at the end of each use to answer a single question with a 7-point scale, indicating the extent to which the service provided useful information. If some users fail to log off the system and invoke the final question, we will send them a query by email.

### Cognitive

#### Attitudes

There are few well-validated outcomes assessments of EBP, knowledge acquisition, or attitude/behavior change. In this study, cognitive elements will be assessed using a previously validated scale containing cognitive and behavioral questions specifically related to EBP [71]. This questionnaire has validated factor structure and construct validity and demonstrated responsiveness to EBP interventions [71]. We have added supplemental questions tailored specifically to Pain PLUS, adapted from the Evidence Updates trial [66] follow-up evaluations, for comparison purposes.

#### Behavioral

Behavior change is the ultimate goal of KT. It will be assessed through self-report, performance tests, and observer-based competency assessments. EBP behaviors will be self-reported using the Behavior Subscale of the Knowledge Attitudes and Behaviour Questionnaire (KABQ) validated in different professions [71]. Similar questions have demonstrated reliability and validity in nurses [76].

#### Skill at accessing research evidence

We will directly measure respondents’ skill in accessing information by providing a clinical scenario where a clinical question needs to be addressed and asking participants to search for research information to address that request. We will monitor their approach to searching and their satisfaction and intention to act upon the information acquired. This test will replicate previous methods used to compare information retrieval by physicians on Clinical Queries versus PubMed [72]. A subset of volunteers (30/profession) will search for information to address two posed clinical questions: one scenario will be a uniform multidisciplinary question (provided to all participants) and the other will be profession specific. Using our tracking software within Pain PLUS, we will be able to identify what search terms are used, what studies are located, the efficiency of their search strategies (*e.g.*, percent of relevant articles, time to find), and effectiveness of their search (quality of the relevant articles located). Volunteers will rate the usefulness of the research located. Our previous study determined that Clinical Queries was more efficient for physicians [72]. In this substudy, we will randomly allocate half of the participants to access through PubMed traditional search versus Clinical Queries, so we can assess whether Clinical Queries is more useful across professions. This subanalysis will provide more detailed and direct data on professional differences in accessing information.

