**Methods:**

Physicians, nurses, occupational/physical therapists, and psychologists (n = 670) will be randomly allocated in a crossover design to receive a pain evidence resource in one of two different ways. Evidence is extracted from medical, nursing, psychology, and rehabilitation journals; appraised for quality/relevance; and sent out (PUSHed) to clinicians by email alerts or available for searches of the accumulated database (PULL). Participants are allocated to either PULL or PUSH + PULL in a randomized crossover design. The PULL intervention has a similar interface but does not send alerts; clinicians can only go to the site and enter search terms to retrieve evidence from the cumulative and continuously updated online database. Upon entry to the trial, there is three months of access to PULL, then random allocation. After six months, crossover takes place. The study ends with a final three months of access to PUSH + PULL. The primary outcomes are uptake and application of evidence. Uptake will be determined by embedded tracking of what research is accessed during use of the intervention. A random subset of 30 participants/ discipline will undergo chart-stimulated recall to assess the nature and depth of evidence utilization in actual case management at baseline and 9 months. A different random subset of 30 participants/ discipline will be tested for their skills in accessing evidence using a standardized simulation test (final 3 months). Secondary outcomes include usage and self-reported evidence-based practice attitudes and behaviors measured at baseline, 3, 9, 15 and 18 months.

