#### Timing of measures

The KABQ will be administered at baseline, 3, 9, 15, and 18 months. Other measures are embedded and distributed over time. CSR will be performed in a subset of 30/group during the first randomization cycle (at baseline and nine months). The skill assessment will be conducted in the final three months of the trial to allow maximum skill development to occur so that our comparisons of professional differences will be less affected by learning curves.

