#### Compliance

Compliance is one of our monitored variables. When participants fail to use an intervention, they are classified in some studies as noncompliant. We view lack of use as a failure of the intervention to meet participant needs. Thus, participants who do not use this service will not be classified as noncompliant or dropouts. Dropouts will be defined as participants who inform us that they no longer wish to participate in the study follow-up process. These participants will not be denied access to the intervention, and we will request permission to continue to use data from the embedded tracking of usage. Each participant will receive a $45 gift card upon completion of at least three survey assessments: baseline, one follow-up (at 3, 9, or 15 months), final assessment. Participants who complete the CSR or the search skills assessment will receive an additional $20 gift card as honorarium for time volunteered.

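### The search-skills sample is random in the Abstract but made up of volunteers in the Methods, and the comparison between professions depends on which rule is used

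*Protocol article*

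**What the plan says.** The Abstract (Methods) describes the sample for the search test in this way: "A different random subset of 30 participants/ discipline will be tested for their skills in accessing evidence using a standardized simulation test". The Methods section headed Skill at accessing research evidence describes the same test with a different source of participants: "A subset of volunteers (30/profession) will search for information to address two posed clinical questions". It uses the same word for them again further on: "Volunteers will rate the usefulness of the research located".

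The only random step that this section describes is the assignment of search tool among people already in the substudy: "we will randomly allocate half of the participants to access through PubMed traditional search versus Clinical Queries".

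Two sections say what the test is for. Skill at accessing research evidence closes with "This subanalysis will provide more detailed and direct data on professional differences in accessing information". Timing of measures places the test in the final three months "so that our comparisons of professional differences will be less affected by learning curves".

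**The concern.** Profession is not randomised, so a comparison of professions is only as good as the way each profession's 30 people were chosen. A random draw from the enrolled participants of each profession lets the 30 stand for that profession's participants. A group that chose to take a search test need not do so, because clinicians who are comfortable with searching may be readier to come forward. If the willing fraction differs between professions, a profession with few takers could be represented by its keener searchers and appear more skilled than it is.

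The test is given only in the final three months, so there is no earlier skill score against which to judge who took part. A reader who relies on the Abstract would not know that the question arises.

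**Working it through.** **1. The two rules side by side.**

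- Number: 30 per discipline in the Abstract, 30 per profession in the Methods. These agree and give 30 × 4 = 120 over the four groups.
- Source: random subset in the Abstract, volunteers (twice) in the Methods. These differ.
- Reconciling text: none. Timing of measures gives only the timing of the skill test. The Compliance section says "Participants who complete the CSR or the search skills assessment will receive an additional $20 gift card as honorarium for time volunteered", but that sentence covers chart-stimulated recall as well, and the Abstract calls the recall sample random too. It therefore does not show which rule applies.

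**2. Which comparisons depend on the rule.**

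- PubMed versus Clinical Queries: allocated at random within the substudy, so its internal validity does not depend on how people entered.
- PUSH versus PULL: randomised in the main trial and not drawn from this substudy.
- Profession versus profession on search skill: not randomised, so it does depend on entry.

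**3. How large could a bias be?** The article gives no figure to reproduce: no derivation of the 30, no acceptance rate, and no correlation between willingness and skill. What follows is an illustration on assumed inputs.

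Let *a* be the fraction of a profession that accepts and *r* the correlation between willingness and skill, both taken as normal. The mean skill of those who accept is raised by *r* × φ(z)/*a* standard deviations, where φ is the standard normal density at the cut-off z that leaves the fraction *a* above it.

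- *a* = 0.20: 0.2800/0.20 = 1.40
- *a* = 0.60: 0.3863/0.60 = 0.644
- *r* = 0.3: 0.3 × 1.40 = 0.42 and 0.3 × 0.644 = 0.19, a gap of about 0.23 SD
- *r* = 0.5: 0.700 − 0.322 = 0.38 SD
- Standard error of a 30 versus 30 comparison: √(2/30) = 0.258 SD

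The chance of a false positive in a two-sided 5% test is Φ(−1.96 + gap/SE) + Φ(−1.96 − gap/SE). It is about 14% for a gap of 0.23 SD and about 31% for 0.38 SD.

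A wider set of assumptions:

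| *r* | acceptance in the two professions | spurious gap (SD) | false-positive rate |
|---|---|---|---|
| 0 | any | 0 | 5% |
| 0.2 | 20% and 50% | 0.12 | 7.5% |
| 0.2 | 20% and 80% | 0.21 | 12.9% |
| 0.4 | 20% and 50% | 0.24 | 15.4% |
| 0.4 | 20% and 80% | 0.42 | 37% |

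If *a* and *r* are equal in the two professions, the shifts cancel and the gap is zero.

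**4. What this calculation measures.** The formula uses only the acceptance fraction. If people are invited in random order and 20% of one profession and 60% of another accept, it gives the same 0.42 and 0.19 SD and the same gap. The illustration therefore shows the effect of unequal acceptance of an optional test. It does not show the difference between a random and a volunteer rule. Random invitation makes acceptance known for each profession; it does not by itself remove the shift.

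**The case against.** The strongest reply is that the two wordings can be squared. A randomly drawn group must still agree to an optional test, and those who agree can fairly be called volunteers. The article is also a condensed account, and the details of a substudy draw are commonly left to the full protocol. The first part is possible, but the article does not say it, and refusals would still need to be reported by profession. The second part would answer an omission. Here the article gives two different descriptions, and one of them has to be corrected.

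Other parts of the reply stand:

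- All participants come through associations, websites, conferences and social media. Even a true random subset would represent the trial's enrollees and not the professions at large.
- The test is one of several measures of professional differences. Tracked use, the evidence-based practice questionnaire and the classification of studies accessed also serve that objective. A reader might infer that the secondary objective as a whole fails, but the article does not support that.
- A reader might infer that places go to whoever responds first. The article gives no order of entry.
- A reader might take 0.23 SD as the expected bias. It follows only from the assumed inputs and, at *r* = 0.3, is below one standard error.
- Weighting 30 people per profession on several covariates could be unstable, so a simple adjustment is the most that should be asked.

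**Conclusion.** The inconsistency is real and stands in the current text: the same test has two rules of entry. If the Methods rule is the one used, the comparison of search skill between professions is a comparison of self-selected groups, and the Abstract describes it wrongly. The point reaches no further than that comparison.

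No size can be put on the bias from the article. Under assumed correlations of 0.2 to 0.5 and the unequal acceptance rates tried above, the spurious gap runs from 0.12 to 0.42 SD. It is zero if willingness is unrelated to skill, or if acceptance and correlation are equal across professions. The article gives no ground for preferring any of these cases. The conclusion that the text must be reconciled does not depend on them.

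**What to change.** State one rule in both the Abstract and the Methods:

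1. Within each profession, list participants in random order, invite in that order until 30 accept, and log everyone invited and everyone who declines. Describe the sample as randomly invited.
2. Report acceptance by profession beside the skill results. Compare acceptors with all participants of their profession on data the plan already collects: the baseline questionnaire, tracked use in the three-month run-in, and comfort with technology.
3. As a sensitivity analysis, repeat the profession comparison with a simple adjustment for those covariates.
4. Keep the caveat that refusal can still bias the comparison. The adjustment helps only as far as these covariates capture willingness.

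If volunteers are to be used instead, delete the word random from the Abstract and label the profession comparison as descriptive and based on a self-selected sample.

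The cost is an invitation list and log, slightly slower filling of the places, and slightly wider intervals in the adjusted analysis. No new measurement is needed. The Trial status section reports more than 70% of the target enrolled and more than 60% of participants at nine months. It does not say how many have reached the final three months, so any tests already done should be reported under the rule actually used for them.

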#### Application of research evidence

We will obtain scores and a more detailed description of actual application of pain research evidence use before and after the intervention by performing chart-stimulated recall (CSR). This approach yields a rich and deep understanding of how evidence is used in practice based on semistructured interviews that probe how/why clinicians make choices about cases retrieved from their own records. A predetermined set of competencies are probed during the interview, and the performance is rated on a 7-point Likert scale. The score provides a quantitative estimate of competency (to use evidence in management of pain in their individual practice). We have successfully coded previous CSR interviews using content-analysis techniques. We have successfully used CSR in a KT study [73] to evaluate competency in clinician decision making, and others have indicated CSR is reliable and valid to assess different types of practice competency in physicians, nurses, and rehabilitation practitioners [73-75,77,78].

#### Timing of measures

The KABQ will be administered at baseline, 3, 9, 15, and 18 months. Other measures are embedded and distributed over time. CSR will be performed in a subset of 30/group during the first randomization cycle (at baseline and nine months). The skill assessment will be conducted in the final three months of the trial to allow maximum skill development to occur so that our comparisons of professional differences will be less affected by learning curves.

#### Mediators of use of evidence/intervention response

It is important to monitor and potentially adjust for important covariates that influence study outcomes. We will measure the following variables for each clinician: baseline knowledge/attitudes towards EBP, years of practice, highest degree, and comfort with technology. Organizational variables will also be collected at baseline, including rural/urban location, clinic size, access to online journals, peer support, administrative support, and management support. These variables will be entered into an analysis of covariance examining pre- and post-intervention effects. Our sample size is sufficiently large that we will be able to assess the primary effects of these variables, as well as interactions between organizational variables and participant variables.

